## Abstract

**Introduction:**

Monomorphic ventricular tachycardia (VT) is a life-threatening condition often observed in patients with structural heart disease. Ventricular tachycardia ablation through radiation therapy (VT-ART) for sustained monomorphic ventricular tachycardia seems promising, effective, and safe. VT-ART delivers focused, high-dose radiation, usually in a single fraction of 25 Gy, allowing ablation of VT by inducing myocardial scars. The procedure is fully non-invasive; therefore, it can be easily performed in patients with contraindications to invasive ablation procedures. Definitive data are lacking, and no direct comparison with standard procedures is available.

**Discussion:**

The aim of this multicenter observational study is to evaluate the efficacy and safety of VT-ART, comparing the clinical outcome of patients undergone to VT-ART to patients not having received such a procedure. The two groups will not be collected by direct, prospective accrual to avoid randomization among the innovative and traditional arm: A retrospective selection through matched pair analysis will collect patients presenting features similar to the ones undergone VT-ART within the consortium (in each center independently). Our trial will enroll patients with optimized medical therapy in whom endocardial and/or epicardial radiofrequency ablation (RFA), the gold standard for VT ablation, is either unfeasible or fails to control VT recurrence. Our primary outcome is investigating the difference in overall cardiovascular survival among the group undergoing VT-ART and the one not exposed to the innovative procedure. The secondary outcome is evaluating the difference in ventricular event-free survival after the last procedure (i.e., last RFA vs. VT-ART) between the two groups. An additional secondary aim is to evaluate the reduction in the number of VT episodes comparing the 3 months before the procedure to the ones recorded at 6 months (from the 4th to 6th month) following VT-ART and RFA, respectively. Other secondary objectives include identifying the benefits of VT-ART on cardiac function, as evaluated through an electrocardiogram, echocardiographic, biochemical variables, and on patient quality of life. We calculated the sample size (in a 2:1 ratio) upon enrolling 149 patients: 100 in the non-exposed control group and 49 in the VT-ART group. Progressively, on a multicentric basis supervised by the promoting center in the VT-ART consortium, for each VT-ART patient enrollment, a matched pair patient profile according to the predefined features will be shared with the consortium to enroll a patient that has not undergone VT-ART.

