## Protocol overview

With current knowledge, it is difficult to set a randomized trial between a population undergoing VT-ART (e.g., in the compassionate setting often applied for patients proposed for such an innovative procedure) and a population not undergone to that. Randomizing a patient’s accrual to VT-ART instead of the conventional option implies that some patients would skip a conventional procedure in favor of a procedure still considerate at least still non-standard, although promising. Multiple, reliable phase I and phase II trials are not available, although case series and at least one phase I/II trial have investigated VT-ART efficacy (1).

Finally, it would be difficult to define two balanced treatment arms that are suitable for a clinical randomized comparison, since patients undergoing VT-ART would have either already received RFA or are unable to receive it, and they have already undergone other standard treatments. On the other hand, setting a single-arm trial would test less efficiently the clinical of VT-ART and could imply the adoption of VT-ART only for worse clinical case presentations.

This multicenter observational study will evaluate the efficacy and safety of VT-ART. Our trial will enroll patients with optimized medical therapy, in whom endocardial and/or epicardial RFA is either unfeasible or fails to control VT recurrence. The trial is set as observational since it indirectly comparing VT-ART with a conventional procedure (i.e., RFA).

Each patient recruited for VT-ART will be profiled according to a predefined list of characteristics that will be circulated within the centers participating to the consortium to collect other patients with a similar profile, not having undergone VT-ART, for final analysis.

The peculiar setting of our trial will avoid precluding VT-ART to patients possibly taking advantage of such a therapeutic option; moreover, it will compare VT-ART with retrospective series not having receive VT-ART anyway. Furthermore, this approach will retrieve otherwise sporadic data about single or limiter case series of each center joining the consortium. This trial is not strictly investigational but can add notable scientific information to the current scenario.

The multicenter setting of this study will allow for faster recruitment of the sample size.

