## Methods/design

Our trial will investigate the effects of administering a single fraction of external beam radiation delivered through SBRT techniques at a dose of 25 Gy on patients with recurrent episodes of VT and in whom optimal medical therapy and previous RFA attempts have failed to provide benefit from VT burden control. We will perform matched pair analysis with dynamic cohorts. We will compare two groups of patients: One that has been treated by all the standard approaches but has not undergone VT-ART and a second group that has also received VT-ART. The entire enrolled group (by multicentric recruitment) will be stratified according to some predefined characteristics and analyzed by matched pair analysis, based on the characteristics of patients treated with VT-ART. Once a patient is enrolled to undergo VT-ART within the multicentric consortium, the search for two patients with similar feature profiles not undergoing VT-ART will be shared.

Matching factors taken into account are summarized in Table 2.

**TABLE 2 T2:** Applied matching factors.

Parameter type	Subgroup options
Etiology of cardiomyopathy*	ICM
	NICM
	ACM
Age*	
Gender*	
BMI	
LVEF*	
NYHA group*	
Ventricular arrhythmia presentations*	Sustained ventricular tachycardia incessant sustained ventricular tachycardia electrical storm
Arrhythmogenic focus anatomical intracardiac location	Based on VE exit by ECG and by the activation map of VT
Diagnostic tools used for scar definition	CT
	MR
	EAM
	ECG
TA volume*	Endocardial electroanatomic substrate mapping area/volume in all cases; epicardial mapping area/volume in the case of 3D epicardial electroanatomic substrate mapping
Heart volume	cc range
Heart-to-TA volume	cc range
Previous use of amiodaron	Y/N
Number of previous RFA attempts*	
Type of previous RFA attempts	endocardial
	epicardial
Unfeasibility to repeat RFA	Y/N
Local recurrence of TA (same area of last RFA)	Y/N
Previous percutaneous stellate ganglion blockade	Y/N

TA, target area by electroanatomical mapping; BMI, body mass index; RFA, radiofrequency ablation; LVEF, left ventricle ejecting fraction; *mandatory matching factor.

Figure 1 depicts the design of the VT-ART study.

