#### Sample size

The calculation of the sample size considered followed assumptions:

-A total of 95% confidence level;-The drop-out rate of 10%;-Expected difference between the two treatments for 3-month and 6-month VT burden in terms of overall response rates: 20% higher in arm including VT-ART compared to the control group;-Power of 80%.

To improve clinically adequate balancing, we will enroll two matching paired patients in the group not undergoing VT-ART for each patient who undergoes VT-ART in a 2:1 ratio, favoring a larger proportion of patients not undergoing the innovative procedure (i.e., VT-ART).

Under these hypotheses, to detect a 20% improvement in the VT burden control rate in the VT-ART group vs. the control group, we calculated the sample size (in a 2:1 ratio) upon enrolling 149 patients: 100 in the non-exposed control group and 49 in the VT-ART group. Progressively, on a multicentric basis supervised by the promoting center in the VT-ART consortium, for each VT-ART patient enrollment, a matched pair patient profile according to the predefined features will be shared with the consortium to enroll two similar patients who have not undergone VT-ART. For enrollment into the control group, recruitment of clinical cases from retrospective case series within the multicentric consortium will also be allowed, with the only condition to be not earlier than 5 years from the enrollment of the matched pair patient in the VT-ART group (to avoid the possible influence of a too early approach for standard procedures).

All statistical analyses will be performed using SPSS^®^ version 25.0 software (©Copyright IBM Corporation 1994, 2017).

Due to the potential difficulty of enrolling the patients through the complete match of all matching factors, a protocol rule will be applied through patient’s collection.

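### The source of matched controls is worded in two ways, and centre is not a matching factor, so centre differences can bias the VT-ART comparison in either direction

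*Protocol article*

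**What the plan says.** The protocol article describes the source of controls in several places.

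- Abstract, Discussion paragraph: the retrospective selection collects patients with features "similar to the ones undergone VT-ART within the consortium (in each center independently".
- Last sentence but for the sample size figures of that same paragraph: each VT-ART patient's profile "will be shared with the consortium to enroll a patient that has not undergone VT-ART".
- Protocol overview: each VT-ART patient is profiled on a list of characteristics "that will be circulated within the centers participating to the consortium to collect other patients with a similar profile".
- Methods/design: once a VT-ART patient is enrolled, "the search for two patients with similar feature profiles not undergoing VT-ART will be shared".
- Sample size: the profile "will be shared with the consortium to enroll two similar patients who have not undergone VT-ART", and "recruitment of clinical cases from retrospective case series within the multicentric consortium will also be allowed".

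On what is matched, Methods/design says "Matching factors taken into account are summarized in Table 2". That table has 18 factors, of which 8 are marked mandatory. The statistical section repeats most of them and adds time intervals. If too few controls are found on all factors, the Sample size section falls back to the mandatory ones. The Registration section adds a final stratification, done globally, without naming its factors.

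**The concern.** Selecting controls within the VT-ART patient's own centre is one design. Selecting them from any centre is another. The first holds operator, equipment, ICD programming habits and follow-up routine roughly constant within a matched set. The second does not, unless centre is matched on or adjusted for.

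The article itself indicates where local practice could matter. The arrhythmia endpoints rest on ICD interrogation. Under Follow-up, prospective RFA patients keep to the VT-ART schedule only as far as need and compliance permit. Retrospective data depend on what was recorded locally, and only patients with data at the set time points enter the final analysis. Centre could thus affect the outcome, how it is ascertained, and who is analysed.

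If the two groups draw on different centres, part of any observed difference in cardiovascular survival, event-free survival or VT burden may be a difference between centres. Matching on patient features does not remove it.

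**Working it through.** **Text check: where controls come from.** The abstract's bracketed phrase has two readings.

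1. Each centre matches only its own VT-ART patients to its own controls. This conflicts with the sharing or circulation of profiles in every other place listed above, including the end of the same paragraph.
2. Each centre searches its own records on its own, but the pool is the consortium. This agrees with the other places and with the Protocol overview, which gives better chances of finding matching profiles as a benefit of the multicentre setting.

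Reading 2 is the more likely, but no sentence confirms it.

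**Text check: is centre controlled elsewhere?**

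| Place | Centre or operator named? |
|---|---|
| Table 2, 8 mandatory factors | No |
| Table 2, 10 other factors | No |
| List in the statistical section | No |
| Mandatory-only fallback (Sample size) | No |
| Global final stratification (Registration) | No |

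So on reading 2, nothing in the stated matching keeps a case and its controls in the same centre.

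**Illustration of size.** The documents give no centre-level rates, so this rests on assumptions.

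Inputs from the Sample size section: 49 VT-ART and 100 control patients, and a planned 20-point difference in VT-burden response. The plan's total of 149 is used only for these group sizes. It cannot be reproduced, as no control rate is stated, and this point does not depend on it.

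Assumptions: no true VT-ART effect; two types of centre whose response rates average 50% and differ by D; a share *a* of VT-ART patients and a share *c* of controls come from the better type; the groups are compared with a pooled two-proportion z-test at two-sided 5%.

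False difference = (*a* − *c*) × D.

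With D = 20 points the rates are 60% and 40%. For *a* = 0.8 and *c* = 0.5:

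- VT-ART: 0.8 × 60 + 0.2 × 40 = 56%
- Control: 0.5 × 60 + 0.5 × 40 = 50%
- False difference: 6 points

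| *a* | *c* | D = 10: false difference; false-positive rate | D = 20 | D = 30 |
|---|---|---|---|---|
| 0.8 | 0.8 | 0; 5% | 0; 5% | 0; 5% |
| 0.8 | 0.5 | 3; 6.3% | 6; 10.5% | 9; 17.6% |
| 1 | 0.5 | 5; 8.8% | 10; 20.7% | 15; 40.6% |
| 1 | 0 | 10; 20.8% | 20; 63.5% | 30; 94.1% |

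The first row is what equal centre mix achieves. Exchanging *a* and *c* reverses the sign, and VT-ART then looks worse than it is. The table concerns VT-burden response. The primary outcome, cardiovascular survival, is open to the same bias, but the documents give nothing from which to size it.

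**The case against.** **The contradiction is thin.** The abstract's sentence itself refers to the consortium, and every other description is consortium-wide. This largely stands: it is an ambiguity to be cleared up, and a reader who infers two firmly opposed rules goes beyond the text. But the likelier reading is the one that leaves centre uncontrolled.

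**Centre adjustment belongs in an analysis plan that is not shown.** This stands for the model terms. It does not stand for the source of controls, which this document fixes and which is settled at enrolment. If the groups overlap little by centre, no later model can separate centre from treatment.

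**There is already some protection.** Data collection is standardised for both groups, retrospective data are extracted at the prospective time points, and previous RFA attempts and scar-definition tools are matching factors. These help, but they do not address operator or local care.

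**Own-centre matching has its own bias.** At a centre offering VT-ART, patients who did not receive it may differ in the reason why. This stands, and it rules out making same-centre controls a requirement.

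**Stronger readings that a reader might infer, and that the documents do not support:**

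- That the 25 to 50% recurrence after RFA, quoted in the final discussion, is a spread between centres, and so implies a 25-point false advantage. It is a reported range in structural heart disease; nothing ties it to centres.
- That some centres will supply controls only. No section says which members deliver VT-ART.
- That the choice of Linac adds to the problem. Linac type is chosen to suit the patient, and it concerns the VT-ART group only. In the Radiotherapy section, only the mapping system is chosen by availability.

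**Conclusion.** The point holds in a limited form. The article leaves unclear whether controls come from the VT-ART patient's centre or from any centre. On the likelier, consortium-wide reading, centre is absent from every stated matching step. A centre difference can then be mistaken for a treatment difference, in either direction.

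The size is unknown. The figures of 6 to 20 points for a 20-point centre difference rest on assumed centre types and assumed imbalance. They show that the bias could reach the planned effect, not that it will. The conclusion assumes that centres differ in ways that affect outcome or its recording, which is plausible but not documented here. It is worth correcting because the source of controls cannot be changed once patients are enrolled.

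**What to change.** 1. State one rule for where controls come from, and use it in the abstract, Protocol overview, Methods/design and Sample size sections.
2. Add centre to Table 2 as a non-mandatory tie-breaker: among candidates who qualify on the other factors, prefer one from the VT-ART patient's centre. Say that it does not count towards the all-factors requirement; otherwise it would tighten the first matching phase and the 60% accrual check.
3. Record the centre of every patient in each matched set. The article says that each centre receives an electronic case report form, but not that centre is a field in it, so this should be confirmed.
4. Report the main comparison with centre accounted for, for example as a random effect, and show how VT-ART and control patients are distributed across centres.
5. Repeat the comparison in same-centre sets as a sensitivity analysis.

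The cost is some wording, possibly one data field, and two analyses. A tie-breaker leaves the pool of eligible controls intact, so accrual and the 1:1 minimum for a final analysis are not put at risk. With 18 factors already in play, ties may be few, and items 3 to 5 would then carry most of the benefit. The same-centre analysis will be smaller and open to confounding by the reason VT-ART was not given, so it should support the main result and not replace it.

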**Conclusion:**

Our trial will provide insight into the efficacy and safety of VT-ART through a matched pair analysis, *via* an observational, multicentric study of two groups of patients with or without VT-ART in the multicentric consortium (with subgroup stratification into dynamic cohorts).

## Background

Monomorphic ventricular tachycardia (VT) is a life-threatening condition often observed in patients with structural heart disease. Recurrence poses a serious threat to both patient survival and quality of life (QoL). The most common cause of recurrent monomorphic VT is the presence of an ischemic scar that induces arrhythmias through re-entry mechanisms. Endocardial and/or epicardial radiofrequency ablation (RFA) represents the gold standard for VT ablation, along with medical therapy.

Stereotactic arrhythmia radioablation (STAR) uses stereotactic body radiation therapy (SBRT) for the ablation of cardiac arrhythmias, which is technically related to any arrhythmia. The present study focuses on ventricular tachycardia ablation through radiation therapy (VT-ART), applying STAR particularly focused on sustained monomorphic ventricular tachycardia.

Stereotactic body radiation therapy using VT-ART delivers focused high-dose radiation in a single fraction of 25 Gy, allowing the ablation of VT by inducing myocardial scars. The procedure is fully non-invasive; therefore, it can be easily performed in patients with contraindications to invasive ablation procedures.

Owing to the highly experimental profile of an innovative procedure such as VT-ART, too little is known to draw definitive conclusions about its efficacy, safety, and long-term results.

## Aims

Our trial aims to assess the benefits of VT-ART for the ablation of VT in patients with optimized medical therapy in whom traditional techniques, namely, RFA, have either failed to control VT recurrence or cannot be performed.

The importance of our trial relies on the identification of new management options for patients who have not responded to traditional ablation techniques or have contraindications to invasive procedures. The efficacy of VT-ART will be indirectly compared through matched pair analysis with a population of patients not treated with VT-ART, thus avoiding setting a randomized controlled trial that is considerable technically demanding and possibly premature in this research field.

## Protocol overview

With current knowledge, it is difficult to set a randomized trial between a population undergoing VT-ART (e.g., in the compassionate setting often applied for patients proposed for such an innovative procedure) and a population not undergone to that. Randomizing a patient’s accrual to VT-ART instead of the conventional option implies that some patients would skip a conventional procedure in favor of a procedure still considerate at least still non-standard, although promising. Multiple, reliable phase I and phase II trials are not available, although case series and at least one phase I/II trial have investigated VT-ART efficacy (1).

Finally, it would be difficult to define two balanced treatment arms that are suitable for a clinical randomized comparison, since patients undergoing VT-ART would have either already received RFA or are unable to receive it, and they have already undergone other standard treatments. On the other hand, setting a single-arm trial would test less efficiently the clinical of VT-ART and could imply the adoption of VT-ART only for worse clinical case presentations.

This multicenter observational study will evaluate the efficacy and safety of VT-ART. Our trial will enroll patients with optimized medical therapy, in whom endocardial and/or epicardial RFA is either unfeasible or fails to control VT recurrence. The trial is set as observational since it indirectly comparing VT-ART with a conventional procedure (i.e., RFA).

Each patient recruited for VT-ART will be profiled according to a predefined list of characteristics that will be circulated within the centers participating to the consortium to collect other patients with a similar profile, not having undergone VT-ART, for final analysis.

The peculiar setting of our trial will avoid precluding VT-ART to patients possibly taking advantage of such a therapeutic option; moreover, it will compare VT-ART with retrospective series not having receive VT-ART anyway. Furthermore, this approach will retrieve otherwise sporadic data about single or limiter case series of each center joining the consortium. This trial is not strictly investigational but can add notable scientific information to the current scenario.

The multicenter setting of this study will allow for faster recruitment of the sample size.

Multicenter recruitment will allow for a more precise assessment of the effects of VT-ART, with the aim of demonstrating that implementing such a procedure is both feasible and safe among centers. Moreover, it will increase the chances to recruit patients with profiles matching the ones in the arm undergone VT-ART.

A standardized data collection has been defined for data regarding both VT-ART and RFA.

The trial will thus both collect prospective and retrospective data about VT-ART (following the predefined standardized data collection). Prospective data collection will be applied within the consortium for the patients referred to VT-ART after the beginning of the trial; retrospective data collection will be allowed for the VT-ART procedure delivered before the formal start of the trial if the data required by the predefined standardized data collection are available for defining the primary and secondary endpoint (see following sections). Similarly, prospective and retrospective data collection will be allowed for data about conventional treatment (i.e., RFA).

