## Outcome measures

The primary outcome is investigating the difference in overall cardiovascular survival among the group undergoing VT-ART and the one not exposed to the innovative procedure.

The primary efficacy endpoint is a statistically significant difference in overall cardiovascular survival between the group undergoing VT-ART and the one not exposed to the innovative procedure; this will be defined in months and calculated from the time of the last procedure (represented by the last RFA for the control group and VT-ART for the innovative one, respectively).

The secondary outcome is evaluating the difference in ventricular event-free (referred to VT/VF, appropriate shock or ATP as recorded by the ICD) survival after the last procedure between the two groups (i.e., the single or last RFA in the control group and VT-ART in the innovative group). The respective endpoint is a statistically significant difference in ventricular event-free survival (in months) after the last procedure between the two groups.

An additional secondary aim is to evaluate the reduction in the number of VT episodes compared to the pre-treatment period between the two dynamic cohorts that will be investigated.

Ventricular tachycardia recurrence will be defined as evidence of monomorphic VT at ICD interrogation (either self-limiting or terminated by appropriate shock therapy or ATP). The number of VT episodes, defined as VT burden, in the 3 months before and after the procedure will then be compared.

The respective secondary endpoint will be evaluated facing 3 months before the last procedure (i.e., either RFA or VT-ART) and 3 months after.

We did set a blanking period after VT-ART before evaluate the effect on VT burden; in a recent study by Kautzner et al., the authors supported the pre-clinical theorem of myocardial apoptosis (up to 3 months post-stereotactic ablation) followed by a creation of fibrotic lesion (6–9 months post-stereotactic ablation) in the irradiated region (5). Consequently, we propose a 3-month-blanking period after the procedure.

Since a blanking period of 3 months after the procedure will be applied, the secondary endpoint will evaluate the number of VT episodes interval accounted for the last 3 months before the procedure and of the 3–6 months after it.

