### Statistical considerations and sample size for matched pair analysis

A descriptive analysis will summarize the total number and stratification of patients with RFA and VT-ART.

We will perform a comparative analysis between RFA and VT-ART in patients with structural heart disease and refractory VT. Each patient who will be treated by VT-ART will be compared with two patients in the control group treated with RFA and best standard care but without VT-ART, on the basis of the following matching factors: Etiology of cardiomiopathy (ICM, NICM, and ACM), ventricular arrhythmia presentations (sustained ventricular tachycardia; incessant sustained ventricular tachycardia; and electrical storm), diagnostic tools used for scar definition (CT, MR, EAM, and ECG), arrhythmogenic focus anatomical intracardiac location (on the basis of VE exit by ECG and by activation map of VT), TA volume (endocardial electroanatomic substrate mapping area/volume in all cases; and epicardial mapping area/volume in case of 3D epicardial electroanatomic substrate mapping), heart volume, heart-to-TA volume, rate number of previous RFA attempts, type of previous RFA attempts (endocardial and epicardial), time (in days) between the first RFA attempt and VT-ART, time (in days) between the last RFA attempt and VT-ART, previous percutaneous stellate ganglion blockade, time (in days) between the percutaneous stellate ganglion blockade and VT-ART previous use of amiodaron, NYHA group, LVEF, BMI, age, and gender.

As mentioned, applied matching factors are summarized in Table 2.

Continuous data will be expressed as mean ± standard deviation, as appropriate, for all variables collected from the entire population or specific subgroups. A comparative analysis for subsequent levels of qualitative variables through the chi-square test and quantitative variables (scores on quality of life) with the *T*-test will be performed.

Non-parametric tests will be provided where the population distribution does not have a known form (normal Gaussian).

The differences in baseline and follow-ups between the same group will be analyzed with repeated measures approach: using the Friedman test and MANOVA for continuous variables and McNemar or Cochran’s *Q*-tests for categorical ones.

The significance of the tests is fixed with *p* < 0.05.

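### Control status (no VT-ART) carries no date, so a retrospective search selects on treatment after time zero: it inflates control event-free survival and usually lowers control cardiovascular survival

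*Protocol article*

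**What the plan says.** The comparator is described in four places, each time by the absence of VT-ART and each time without a date.

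- Protocol overview: profiles are circulated "to collect other patients with a similar profile, not having undergone VT-ART, for final analysis". The same section says of the design that "it will compare VT-ART with retrospective series not having receive VT-ART anyway".
- Methods/design sets out two groups: "One that has been treated by all the standard approaches but has not undergone VT-ART and a second group that has also received VT-ART".
- Statistical considerations: each VT-ART patient is compared with two controls "treated with RFA and best standard care but without VT-ART".
- Sample size: the consortium is asked "to enroll two similar patients who have not undergone VT-ART". Retrospective cases are allowed "with the only condition to be not earlier than 5 years from the enrollment of the matched pair patient in the VT-ART group".

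Under Outcome measures, survival is counted from the last procedure, "represented by the last RFA for the control group and VT-ART for the innovative one". The article does not say what happens to a control who later receives VT-ART. The term dynamic cohorts appears several times but is not explained and supplies no such rule.

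**The concern.** A control's clock starts at the last RFA, but whether the patient qualifies as a control depends on something that may happen later. Under Aims and Populations, one of the two routes to VT-ART is VT that recurs despite RFA. A patient who has RFA, recurs and then has VT-ART was a standard-care patient for the whole interval between the two procedures. A centre searching its records afterwards will not list that patient as without VT-ART.

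The comparator then loses patients because of a treatment given in response to an outcome. The comparison no longer estimates VT-ART against standard care in similar patients. The distortion reaches both the primary outcome and the first secondary outcome, and not necessarily in the same direction. On cardiovascular survival the likelier error favours a procedure that the Background itself calls highly experimental.

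**Working it through.** The plan has no figure of its own on this point. The check is first textual and then a simulation of what the rule does.

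**1. Can VT-ART-free status be judged after time zero?** Yes. The control's time zero is the last RFA. The search starts when a VT-ART patient enrols, and a retrospective control may date from up to 5 years before that enrolment. Even if the status is read at matching rather than over the patient's whole record, it can be read years after the control's own time zero. Only prospectively enrolled controls escape this, and for them later VT-ART is not addressed. The Statistical considerations also list the interval from last RFA to VT-ART as a matching factor. A control has no such value unless an index date is assigned.

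**2. Mechanism.** Let S(t) be survival in all RFA patients followed without VT-ART, q the share removed because they later reach VT-ART alive, and A(t) survival at t in those removed. Survival among those kept is

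K(t) = [S(t) - q·A(t)] / (1 - q).

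K is below S whenever A exceeds S. To be removed, a patient must live from RFA to VT-ART, which pushes A up early on. A higher death risk after recurrence pushes A down later. For event-free survival at the end of the window, A = 0, because everyone removed has recurred, so K is above S.

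**3. Assumed inputs.** The Discussion gives recurrence after RFA of 25-50% without a time horizon; 12 months is assumed. The rest is also assumed: 12-month cardiovascular death before recurrence of 5% or 10%; death hazard multiplied by 1, 2 or 4 after recurrence; 20% or 50% of recurrers referred to VT-ART; mean lag of 1 or 6 months; constant hazards; 36 months of follow-up (Follow-up section). Event-free means neither VT recurrence nor cardiovascular death. That gives 2 × 2 × 3 × 2 × 2 = 48 scenarios, each with 1,000,000 simulated RFA patients.

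**4. Worked cases** (25% recurrence, 10% death, 50% referred, 1-month lag).

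- Event-free survival, doubled hazard: S(12) = 0.75 × 0.90 = 0.675 and S(36) = 0.675³ = 0.308. With q = 0.25, K(36) = 0.308 / 0.75 = 0.41 (simulated 0.407), a rise of about 10 points.
- Cardiovascular survival at 12 months, doubled hazard: S = 0.888 and K = 0.865. So A = (0.888 - 0.75 × 0.865) / 0.25 = 0.96. Those removed survive better than those kept, and the control figure falls by 2.3 points.
- Cardiovascular survival at 36 months, fourfold hazard: q = 0.24, S = 0.562, K = 0.578. So A = (0.562 - 0.76 × 0.578) / 0.24 = 0.51. Those removed now survive worse, and the control figure rises by 1.6 points.

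**5. Range over all scenarios** (shift in the control figure, percentage points; the last digit carries simulation error of about 0.1).

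| Outcome | 6 months | 12 months | 36 months |
|---|---|---|---|
| Event-free survival | +0.6 to +3.7 | +1.1 to +6.6 | +1.3 to +13.1 |
| Cardiovascular survival | not summarised | -0.3 to -4.6 | -5.9 to +1.6 |

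Event-free survival rises in every scenario. Cardiovascular survival falls in every scenario at 12 months. At 36 months it rises only where the fourfold hazard is combined with 25% recurrence.

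**The case against.** The strongest reply is that the wording can mean VT-ART-free at enrolment, and that the text nowhere says never. That is fair: a lifetime exclusion is an inference. It rescues prospective controls only. For a retrospective control, status at matching is still status after time zero.

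Second, Table 1 already requires refractory VT, and matching covers the number of previous RFA attempts (mandatory) and, under full matching, local recurrence and whether RFA can be repeated. Patients who never had RFA can also reach VT-ART, and they do not leave an RFA control pool. All this narrows the selection. It does not remove it, because among eligible patients those whose last RFA fails and who are referred onward are still the ones lost.

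Third, VT-ART is rare: the plan foresees 49 such patients, so the referred share may be below 20%. That stands, and the shifts would shrink accordingly.

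Fourth, handling of crossover could sit in an analysis plan. The analysis of later VT-ART could, but who is searched for is an enrolment rule, and an analysis plan cannot readily recover controls who were never collected.

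Two stronger readings are tempting, and the document does not support them.

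- A reader might infer that controls simply look too good, so that the bias works against VT-ART. That fails for the primary outcome because of the survival needed to reach VT-ART.
- A reader might compute the recurrence left among controls as r(1 - f)/(1 - rf). Then 50% becomes 44% (f = 20%) or 33% (f = 50%), and 25% becomes 21% or 14%. Setting these 4 to 17 points against the planned 20-point difference is not valid. The formula has no time axis, f is assumed, and the 20 points concern VT burden response at 3 and 6 months, not cumulative recurrence.

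**Conclusion.** The concern holds in this form: control status is undated, time zero is the last RFA, and a retrospective search applied as written selects on later treatment driven by the outcome. It overstates control event-free survival. It usually understates control cardiovascular survival and so favours VT-ART on the primary outcome, but that sign is not certain and depends on the death risk after recurrence.

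The tabulated shifts are illustrations. They rest on the assumed referral share, lag, death rates and recurrence horizon, none of which the protocol gives, and on a population not restricted by Table 1 or by matching. The document also does not establish that crossover controls would be dropped or counted twice; keeping them as controls is equally open, because it states no rule.

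**What to change.** In Protocol overview, Methods/design and Sample size, with Statistical considerations aligned, define a control as a patient who is VT-ART-free at his or her own time zero, whatever happens later. Preferably, set that time zero at the same interval since last RFA as in the matched VT-ART patient and start follow-up there. This also gives the interval matching factor a meaning for controls, but the time origin under Outcome measures must then be changed to match.

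For controls who later receive VT-ART:

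- keep them in the control group and count every event before that date, including the recurrence that led to referral;
- censor at VT-ART, using inverse-probability-of-censoring weights for cardiovascular survival, since plain censoring at a treatment triggered by recurrence is informative;
- add a sensitivity analysis that keeps them as controls for all follow-up;
- state that their time after VT-ART is not used in both groups in the main comparison.

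The cost is protocol wording, one extra date per control in the case report form, some censored control follow-up and a little more analysis. No extra patients are needed, and the pool of eligible controls grows.
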